**STUDY SYNOPSIS**

| **Protocol Title** | Randomised controlled trial comparing efficacy and safety of high versus low Low-Molecular Weight Heparin dosages in hospitalised patients with severe COVID-19 pneumonia and coagulopathy not requiring invasive mechanical ventilation (COVID-19 HD) |  |
| --- | --- | --- |
| **Clinical Trial Phase** | III |  |
| **Study Site** | Azienda Ospedaliero-Universitaria di Modena  Ospedale Policlinico di Modena  [name] |  |
| **Background and Rationale** | In December 2019, a cluster of acute respiratory illnesses caused by SARS-CoV-2 virus occurred in Wuhan, Hubei Province, China. The disease has rapidly spread from Wuhan to many other countries worldwide, soon becoming a global health emergency.  Pneumonia is the most frequent and serious complication of COVID-19, the disease that results from SARS-CoV-2 infection.  The pathogenesis of SARS-CoV-2 infection in humans remains unclear, although it is very likely that the most severe manifestations of COVID-19 may be linked to host-pathogen interaction immune mechanisms.  Both coagulation factors and platelets are directly implicated in the modulation of the host immune response, displaying proinflammatory functions independent of their hemostatic effects.  Heparin, being an anticoagulant that also possesses immunomodulatory properties, represents a promising drug for lowering immune response and hypercoagulability observed in COVID-19 patients. Its use at prophylactic doses has been shown to be associated with a reduced 28-day mortality in severe COVID-19 patients with coagulopathy. However, no evidence is still available as to whether higher doses of heparin can improve the prognosis of more severe COVID-19 patients without affecting the safety aspects related to bleeding. |  |
| **Study Period** | June 2020 – June 2021 |  |
| **Study population** | Hospitalized patients with severe COViD-19 pneumonia and coagulopathy not requiring invasive mechanical ventilation. |  |
| **Primary Study Objective(s)** | To assess whether high doses of Low Molecular Weight Heparin (LMWH) (ie. Enoxaparin 70 IU/kg twice daily) compared to standard prophylactic dose (ie, Enoxaparin 4000 IU once day) are:  a) more effective to prevent clinical worsening, defined as the occurrence of at least one of the following events, whichever comes first, during hospital stay:   1. Death 2. Acute Myocardial Infarction [AMI] 3. Objectively confirmed, symptomatic arterial or venous thromboembolism [TE] 4. Need for either non-invasive - Continuous Positive Airway Pressure (Cpap) or Non-Invasive Ventilation (NIV) - or invasive mechanical ventilation for patients who are in standard oxygen therapy by delivery interfaces at randomisation 5. Need for invasive mechanical ventilation for patients who are in non-invasive mechanical ventilation at randomisation 6. Similar in terms of major bleeding risk during hospital stay |  |
| **Secondary Study**  **Objectives** | To assess whether high doses of Low Molecular Weight Heparin (LMWH) (ie. Enoxaparin 70 IU/kg twice daily) compared to standard prophylactic dose (ie, Enoxaparin 4000 IU once day) differ in terms of the following events occurring during hospital stay:   1. Laboratory parameters of disease severity, including: 2. D-dimer level 3. Plasma fibrinogen levels 4. Mean Platelet Volume 5. Lymphocyte/Neutrophil ratio 6. IL-6 plasma levels 7. Clinically relevant non-major bleeding 8. Death during hospital stay and at 30 days 9. Acute Myocardial Infarction [AMI] 10. Objectively confirmed, symptomatic arterial or venous thromboembolism [TE] 11. Need for either non-invasive - Continuous Positive Airway Pressure (Cpap) or Non-Invasive Ventilation (NIV) - or invasive mechanical ventilation for patients, who are in standard oxygen therapy by delivery interfaces at randomisation 12. Need for invasive mechanical ventilation for patients, who are in non-invasive mechanical ventilation at randomisation | |
| **Statistical Considerations**  **& Sample Size** | **Statistical Considerations**  The efficacy will be assessed by estimating the difference between the two treatment arms in the proportion of participants experiencing clinical worsening during their hospital stay.  Safety will be assessed by estimating the difference between the two treatment arms in the proportion of participants who experience at least one bleeding event (major or non-major) during their hospital stay.  Relative risk (RR) will be used as measure of association, which will be reported with its 95% confidence interval.  The differences between the two arms in the variation of:   1. D-dimer level 2. Plasma fibrinogen levels   3) Mean platelet Volume  4) Lymphocyte/Neutrophil ratio  5) IL-6 plasma levels  at 3 time points (at randomization, at 48 hours and 96 hours) will be assessed.  These outcomes will be compared by using their mean values and summary indicators.  Overall survival, survival free from any cardiovascular event, such as Acute Myocardial Infarction [AMI], Objectively confirmed, symptomatic arterial or venous thromboembolism [TE] and survival free from need for either non-invasive or invasive mechanical ventilation will be also estimated. They will be reported by using Kaplan-Maier curves and compared by using hazard ratio (HR).  **Sample size**  300 participants will be needed to detect a relative reduction of 50% of clinical worsening. We hypothesized that the percentage of participants who experience clinical worsening in the LMWH low dose group would be around 25-30% and set an alpha error of 0.05 and beta-error of 0.20. | |
| **Treatment Schedule** | **Control group (Low Dose):** Enoxaparin (Inhixa®) 4000 IU subcutaneously once daily.  **Intervention group (High dose**): Enoxaparin (Inhixa®) 70 IU/kg subcutaneously twice daily.  Participants will receive the dose of Enoxaparin according to the protocol until the occurrence of at least one of the following events:   1. One of the events included in the primary outcome 2. Hospital discharge 3. Any adverse events and clinical condition requiring interruption of the scheduled intervention according to the judgement of the physician in charge | |
| **Inclusion criteria** | Patients admitted to the hospital with COVID-19 confirmed by PCR test on throat swab samples, and with severe pneumonia plus coagulopathy, defined as the presence of at least one clinical and one laboratory criteria (see table below)   \| **Clinical criteria**  **(at least one)** \| **Laboratory criteria and SIC score**  **(at least one)** \| \| --- \| --- \| \| 1) Respiratory Rate ≥ 25 breaths /min \| 1) D-dimer > 4 times the upper level of normal reference range \| \| 2) Arterial oxygen saturation ≤ 93% at rest in room air \| 2) Sepsis-Induced Coagulopathy (SIC) score > 4 \| \| 3) PaO2/FiO2 ≤ 300 mmHg \|  \| | |

| **Main Exclusion Criteria** | 1. Age < 18 and > 80 years 2. Invasive ventilation 3. Thrombocytopenia (platelet count < 80.000 mm^3^) 4. Coagulopathy: INR >1.5, aPTT ratio >1.4 5. Impaired renal function (eGFR by CKD-EPI Creatinine equation < 30 ml/min) 6. Known hypersensitivity to enoxaparin 7. History of heparin induced thrombocytopenia 8. Presence of an active bleeding or a pathology susceptible of bleeding in presence of anticoagulation (e.g. recent haemorrhagic stroke, peptic ulcer, malignant tumors at high risk of haemorrhages, recent neurosurgery or ophthalmic surgery, vascular aneurysms, arteriovenous malformations) 9. Concomitant anticoagulant treatment for other indications (e.g. atrial fibrillation, venous thromboembolism, prosthetic heart valves) 10. Concomitant double antiplatelet therapy 11. Administration of therapeutic doses of LMWH, fondaparinux, or unfractionated heparin (UFH) for more than 72 hours before randomization; prophylactic doses are allowed 12. Pregnancy or breastfeeding or positive pregnancy test 13. Presence of other severe diseases impairing life expectancy (e.g. patients are not expected to survive 28 days given their pre-existing medical condition) 14. Lack or withdrawal of informed consent |
| --- | --- |

**1.0 INTRODUCTION**

**1.1 BACKGROUND AND RATIONALE**

In December 2019, a cluster of acute respiratory illnesses caused by SARS-CoV-2 virus occurred in Wuhan, Hubei Province, China. The disease has rapidly spread from Wuhan to many other countries worldwide, soon becoming a global health emergency.

Although most patients have mild manifestations and good prognosis after infection, some patients develop severe symptoms and die from multiple organ complications. Pneumonia is the most frequent and serious complication of COVID-19, the disease that results from SARS-CoV-2 infection [1,2].

The pathogenesis of SARS-CoV-2 infection in humans remains unclear, although it is very likely that the most severe manifestations of COVID-19 may be linked to host-pathogen interaction immune mechanisms. [3]

SARS-CoV-2 infection seems to induce in most critical cases an excessive and aberrant hyper-inflammatory host immune response that is associated with a so-called "cytokine storm", characterized by plasma increase of infection-related biomarkers and of many cytokines and chemokines documented in many observational studies. [4]. A pro-thrombotic derangement of the haemostatic system has been reported in most severe forms of COVID-19 infections [5-10].

This finding is consistent with the activation of a coagulative cascade primed by inflammatory stimuli already observed in many other forms of sepsis. [11] Indeed, several studies have demonstrated the close interconnection between thrombosis and inflammation, two processes mutually reinforcing each other [12-14]. Both coagulation factors [15] and platelets [16] are directly implicated in the modulation of the host immune response, displaying proinflammatory functions independent of their haemostatic effects.

From a clinical perspective, the extent of the derangement in coagulation parameters in patients affected by severe COVID-19 pneumonia was associated to a poor prognosis. [17,18] In these patients, Low Molecular Weight Heparin (LMWH) at doses registered for prevention of venous thromboembolism (VTE), i.e. Enoxaparin 4000 IU subcutaneously daily, has been proven to be associated with a reduced risk of death [19] and is currently recommended by World Health Organization [20] and by several Scientific Societies [18-25].

However, some issues about the use of LMWH in COVID-19 pts require further clarification.

First, the reported incidence of venous thromboembolism in COVID-19 patients is strikingly variable, ranging from 0% to about 8% in general wards [26,27], and from 16% to 35% in the ICU setting, often despite adequate LMWH prophylaxis [28-35].

This finding prompted some Authors to raise the question whether the pulmonary vessels occlusions observed in COVID-19 patients result from embolization of a deep-venous thrombosis or from a thrombotic microangiopathy affecting the pulmonary vascular bed [28].

On this regard, it has been suggested that the diffuse bilateral pulmonary inflammation observed in COVID-19 is associated with a novel pulmonary-specific pathophysiological entity termed pulmonary intravascular coagulopathy (PIC), distinct from Disseminated Intravascular Coagulation. [36]

LMWH has also been shown to protect glycocalyx from shedding, displaying anti-inflammatory and immunomodulatory properties. [37] Of note, in vitro and in vivo experimental studies have shown that human coronaviruses utilize heparin sulphate proteoglycans for attachment to target cells [38], suggesting a role for heparin in the therapeutic armamentarium against COVID-19 [39].

On these grounds, it is conceivable that doses of LMWH higher than those used for VTE prevention in acutely ill medical patients, might improve anti-inflammatory activity, mitigate cytokines storm and improve the disease prognosis.

However, evidence is not yet available as to whether higher doses of heparin can improve the prognosis of more severe COVID-19 patients without affecting the safety related to bleeding.

Indeed, the paper from Tang and colleagues showed that the use of LMWH reduces the 28-day mortality only in patients with the most severe degree of coagulopathy, as assessed by a Sepsis-Induced Coagulopathy (SIC) score >4 or d-dimer levels >6-fold the upper limit of normal, whereas a non-significant trend towards a negative effect of the treatment was observed in the less severely affected ones [19].

This finding highlights the need for a very careful selection of patients’ population in designing trials on this setting, because of the narrow margin on the risk-benefit ratio.

We report here the design of the COVID-19 HD study, a randomized trial comparing high doses of Low Molecular Weight Heparin (LMWH) (ie. Enoxaparin 70 IU/kg twice daily) with standard prophylactic dose (ie, Enoxaparin 4000 IU once day) for the treatment of severe pneumonia and coagulopathy in hospitalised patients with COVID19 not requiring invasive mechanical ventilation (IMV).

**1.1.3 Benefits of the use LMWH**

As reported in the previous section, the use of LMWH or Unfractionated Heparin (UFH) at prophylactic doses has been shown to be associated with a reduced mortality at 28 days in COVID-19 patients with severe pneumonia and Sepsis Induced Coagulopathy (SIC) score ≥4 (40.0% vs 64.2%, P=0.029), or D-dimer > 6-fold of upper limit of normal (32.8% vs 52.4%, P=0.017 [11]. This finding is consistent with the well-known immune-modulatory properties and protective action of glycocalyx from shedding displayed by heparin. [15].

However, no evidence is available about the clinical question of whether higher doses of LMWH improve the prognosis of more severe COVID-19 patients.

**1.2 STUDY OBJECTIVE**

To assess whether high doses of Low Molecular Weight Heparin (LMWH) (i.e. Enoxaparin 70 IU/kg twice daily) compared to standard prophylactic dose (i.e., Enoxaparin 4000 IU once day) are:

1. more effective to prevent clinical worsening, defined as the occurrence of at least one of the following events, whichever comes first:
2. Death
3. Acute Myocardial Infarction [AMI]
4. Objectively confirmed, symptomatic arterial or venous thromboembolism [TE]
5. Need for either non-invasive - Continuous Positive Airway Pressure (Cpap) or Non-Invasive Ventilation (NIV) - or invasive mechanical ventilation for patients, who are in standard oxygen therapy by delivery interfaces at randomisation
6. Need for invasive mechanical ventilation for patients, who are in non-invasive mechanical ventilation at randomisation
7. Similar in terms of major bleeding risk

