**2.4.3 Primary safety endpoint:**

Major bleeding, defined as an acute clinically overt bleeding associated with one or more of the following:

- Decrease in haemoglobin of 2 g/dl or more;
- Transfusion of 2 or more units of packed red blood cells;
- Bleeding that occurs in at least one of the following critical sites [intracranial, intraspinal, intraocular (within the corpus of the eye; thus, a conjunctival bleed is not an intraocular bleed), pericardial, intra-articular, intramuscular with compartment syndrome, or retroperitoneal];
- Bleeding that is fatal (defined as a bleeding event that was the primary cause of death or contributed directly to death);
- Bleeding that necessitates surgical intervention

Time to the occurrence of each of these events will be recorded.

Each of these events will be analysed as a binary outcome and as a time-to-event one.

- - 1. **Secondary safety endpoint:**

Clinically Relevant non-major bleeding, defined as an acute clinically overt bleeding that does not meet the criteria for major and consists of:

1. Any bleeding compromising hemodynamics
2. Spontaneous hematoma larger than 25 cm^2^, or 100 cm^2^ if there was a traumatic cause
3. Intramuscular hematoma documented by ultrasonography
4. Epistaxis or gingival bleeding requiring tamponade or other medical intervention
5. Bleeding from venipuncture for >5 minutes
6. Hematuria that was macroscopic and was spontaneous or lasted for more than 24 hours after invasive procedures
7. Hemoptysis, hematemesis or spontaneous rectal bleeding requiring endoscopy or other medical intervention
8. Any other bleeding requiring temporary cessation of a study drug.

Time to the occurrence of each of these events will be recorded.

Each of these events will be analysed as a binary outcome and as a time-to-event one.

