**2.4.4 Risk/benefit Ratio**

Recently published data have shown that the use of low-dose heparin in patients admitted to hospital with COVID-19 and severe pneumonia and coagulopathy, reduces mortality from about 60% to about 30%.

We assume that higher doses of LMWH in these patients might be more effective than low doses in reducing the risk of clinical worsening. At the same time, we are aware that the administration of high doses of LMWH might be associated with a higher risk of bleeding. However, we think that the possible increased risk of major bleeding could be negligible, as Wein et al [16] reported a risk of major bleeding between 1.4% and 2.29% with low doses of LMWH, whereas Pengo et al [17] reported a 2.7% risk when LMWH was given at high doses.

We think that on these premises, the risk/benefit of the intervention is favourable for severe COVID-19 patients and allows us to consider the study worth carrying out.

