**4.2 Statistical Methods**

All patients enrolled in the study will be entered in the full analysis set independently of his/her treatment time. The intention to treat population will be considered for primary analysis. A descriptive statistical analysis will be carried out to summarise every relevant variable. At baseline, categorical data will be summarised by using counts and percentages, whilst continuous variables will be presented using the number of patients, mean, standard deviation, median, minimum, and maximum. Comparison between binary outcomes will be performed by using Relative Risks (RRs), whereas for continuous data, the difference of means (DMs) will be used. Comparisons involving time to event data will be displayed by using Kaplan-Maier survival curves and summarised by Hazard Ratios (HRs).

All measures of association will be presented with their 95% confidence interval. A result will be considered as statistically significant if its p-values will be less than 0.05 (5%).

The analyses will be performed by using STATA software.

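### The primary objective asks whether high dose is 'similar' in major bleeding, but similarity is undefined and about 2-3 versus 4 expected events cannot show it; one synopsis sentence also assesses a different bleeding endpoint

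*Protocol*

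**What the plan says.** Section 1.2 of the protocol asks whether high dose, besides preventing clinical worsening better, is "Similar in terms of major bleeding risk". The synopsis places the same aim under Primary Study Objective(s): "Similar in terms of major bleeding risk during hospital stay". Section 2.4.3 makes this the primary safety endpoint ("Major bleeding, defined as an acute clinically overt bleeding associated with one or more of the following"). Clinically relevant non-major bleeding is the secondary safety endpoint in section 2.4 and a secondary objective in the synopsis.

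The synopsis row on statistical considerations differs. It says that safety is assessed by the difference between arms in the "proportion of participants who experience at least one bleeding event (major or non-major) during their hospital stay".

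For analysis, section 4.2 uses relative risks for binary outcomes and hazard ratios for time-to-event outcomes. It adds: "All measures of association will be presented with their 95% confidence interval". Its only decision rule is significance at p below 0.05.

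Section 2.6 sizes the trial at 300, randomised 1:1, for a 50% relative reduction from a 25-30% control rate of clinical worsening. (The last clause of 2.6 names death, but the control rate is that of clinical worsening, and the synopsis gives the same figures for clinical worsening.) No figure is given for bleeding.

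Section 2.4.4 cites major bleeding of 1.4-2.29% at low dose and 2.7% at high dose, and says that "the possible increased risk of major bleeding could be negligible".

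**The concern.** Similarity is a claim in its own right. It needs a stated largest acceptable excess and a confidence limit that excludes it. The protocol sets the objective without either, on an endpoint for which it expects only a handful of events. The one rule it supplies asks whether a difference is significant. With so few events, non-significance says little, because a material excess of bleeding would usually pass unnoticed.

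This matters because the risk/benefit argument in 2.4.4 rests partly on the excess being negligible. A report of similar bleeding would appear to confirm that argument when the data could not.

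The differing synopsis sentence adds a second question: whether the safety conclusion rests on major bleeding or on any bleeding. Non-major events could dominate the combined count, and the two comparisons need not agree.

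**Working it through.** **Inputs.** 150 per arm and two-sided 5% (2.6); major bleeding 1.4-2.29% at low dose and 2.7% at high dose (2.4.4). Non-inferiority margins are assumed, because the protocol states none.

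**1. The plan's own figure.** With control rate 25%, treated rate 12.5% and pooled rate 18.75%:

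n per arm = [1.96·√(2·0.1875·0.8125) + 0.8416·√(0.25·0.75 + 0.125·0.875)]² / 0.125² = (1.0819 + 0.4586)² / 0.015625 ≈ 151.9, so 152 per arm and 304 in total.

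The stated 300 is reproduced to within 2%, from clinical worsening alone.

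**2. Expected major bleeds per arm.** Low dose: 150 × 0.014 = 2.1 to 150 × 0.0229 = 3.4. High dose: 150 × 0.027 = 4.05.

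**3. Power of a difference test.** These are exact binomial sums. The first figure in each cell is Fisher's test and the second is the uncorrected chi-square.

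| True high-dose rate | Low dose 1.4% | Low dose 2.29% |
| --- | --- | --- |
| 2.7% (protocol) | 4-11% | 2-5% |
| Doubling | 5-12% | 11-18% |
| Tripling | 18-29% | 36-48% |

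A true doubling is therefore missed 82-95% of the time and a true tripling 52-82%. Power reaches 80% only at a true relative risk of about 5.6-6.3 (from 1.4%) or 4.2-4.6 (from 2.29%).

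**4. A typical result: 3 versus 4 events.**
- Risk difference = 1/150 = 0.67 points. SE = √(0.02·0.98/150 + 0.0267·0.9733/150) = 0.01743. 95% CI: 0.67 ± 3.42, or -2.7 to +4.1 points.
- Relative risk = 4/3 = 1.33. SE of the log = √(1/3 - 1/150 + 1/4 - 1/150) = 0.755. 95% CI: 0.30 to 5.9.

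This result is compatible with less than a third of the bleeding and with nearly six times as much.

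**5. Smallest margin with 80% power at 150 per arm** (one-sided 2.5%). Margin = (pH - pL) + (1.96 + 0.8416)·√[pL(1-pL)/150 + pH(1-pH)/150], where pL and pH are the low-dose and high-dose rates.
- Equal rates, 1.4%: 2.8016 × 0.01357 = 3.8 points.
- Equal rates, 2.29%: 2.8016 × 0.01727 = 4.8 points.
- 1.4% versus 2.7%: 1.3 + 2.8016 × 1.6345 = 5.9 points.
- 2.29% versus 2.7%: 0.41 + 2.8016 × 1.8009 = 5.5 points.

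These margins are about 2 to 4 times the low-dose rate itself.

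**6. The endpoint, place by place.** Section 1.2, the synopsis objectives and section 2.4.3 all make major bleeding primary. The synopsis statistical row alone uses major or non-major bleeding.

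**The case against.** The strongest reply is that estimation is already planned. The synopsis speaks of estimating the difference between arms, and 4.2 promises a 95% CI on every measure of association. A safety endpoint not powered for equivalence is not in itself a defect, and a margin could be left to a statistical analysis plan.

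The first part stands: the planned interval is the right output. But no bound is attached to it, so it cannot answer the question that the objective asks. Nor would a later margin rescue the claim unless it were wide. At an assumed 3 points and equal true rates, the total needed is 482 (at 1.4%) to 782 (at 2.29%), against 300.

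Several stronger readings are tempting but not supported:
- *The plan offers only a significance test and will read non-significance as similarity.* No section says so; the intervals are planned.
- *Almost any result would pass.* It would not. Against 2 low-dose events, 10 high-dose events (Fisher) or 9 (chi-square) are significant; against 3, 12 or 10.
- *A tripling would very likely be missed.* Across the protocol's rates it is missed 52-82% of the time, which is more likely than not.
- *No margin is feasible.* At equal true rates of 1.4%, a 4-point margin needs 272 in total.
- *Bleeding is a co-primary endpoint, or the synopsis sets a rival primary one.* The protocol separates primary efficacy from primary safety, and the differing synopsis sentence does not call its endpoint primary.
- *Follow-up after the assigned dose stops pulls the arms together.* The protocol gives no basis for the direction or size of such an effect.

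**Conclusion.** The point holds as an objective that is wrong as written. Followed as it stands, the plan cannot support a conclusion of similar major bleeding: similarity is undefined, and about 2-3 versus 4 expected events would support it with 80% power only at margins of roughly 4-5 points if the true rates are equal, or 5.5-5.9 points at the protocol's own rates. The inconsistency in the safety endpoint is real but confined to one synopsis sentence.

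The figures assume that the rates cited in 2.4.4 apply to this population and that all 150 per arm are analysed. The ranges also reflect that the protocol names no specific test.

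**What to change.** In 1.2 and in the synopsis primary objective, replace the similarity wording with: *to estimate the difference in major bleeding between arms with its 95% CI; a non-significant difference will not be interpreted as similarity.*

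In the synopsis statistical considerations, change the safety sentence so that major bleeding is the primary safety comparison, and major plus clinically relevant non-major bleeding is secondary.

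The cost is a wording amendment. The sponsor gives up the word 'similar'; no patients are added and the planned intervals stay as they are. If the sponsor wishes to keep the similarity claim, the protocol needs a justified margin, a rule based on the confidence limit and a sample size to match.
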